### Quality control and data management

Data will be collected using paper Case Record Forms (CRFs). Prior to participant enrollment, all study personnel will receive standardized training to ensure proper understanding of study procedures and data recording requirements. Data will be recorded by trained investigators in real time, followed by independent double-checking by two individuals to ensure completeness and logical consistency of the forms. Data entry will be performed using a double-entry system. Upon completion, consistency checks will be conducted. Any discrepancies or abnormal values will be traced back to the original records for verification and correction. All participants will be identified using unique study codes. The linkage between personal information and study codes will be stored separately, accessible only to authorized research staff for necessary identification. All paper-based data will be securely stored in designated cabinets, with no access granted to unauthorized personnel. The hospital’s Ethics Committee will oversee the data collection and management process to ensure compliance with ethical guidelines and data protection requirements.

To promote participant retention and adherence to the follow-up schedule, regular reminders (e.g., phone calls or text messages) will be provided before each study visit. Participants and their guardians will receive educational support and periodic feedback regarding progress. Concurrent health education sessions during visits will reinforce engagement and study goal understanding. For participants who withdraw or deviate from the intervention protocol, efforts will be made to collect primary and secondary outcome data at all available time points, particularly at the 12-week and 24-week assessments.

### Oversight and monitoring

Given the minimal risk nature of the intervention and the small, single-center design, a formal Data Monitoring Committee (DMC) was deemed unnecessary. No formal auditing is planned. Study oversight will be maintained by the principal investigator and co-investigators. The study will not have a separate coordinating center, steering committee, or endpoint adjudication committee. The hospital’s Medical Ethics Committee will provide ethical oversight, ensuring that the study is conducted in compliance with ethical guidelines. The Research Administration Department of the hospital will monitor the administrative and financial compliance of the study.

### Protocol amendments

Any important protocol amendments (e.g., to eligibility criteria, outcomes, or analysis methods) will be promptly communicated to all relevant parties, including investigators, the Medical Ethics Committee, trial registries, and participants as appropriate.

### Statistical analysis

Data analysis will follow the intention-to-treat (ITT) principle and will be conducted under blinded conditions. For the primary endpoint (between-group difference in BMI *z*-score change at week 12) and secondary endpoints involving continuous variables (BMI *z*-scores, waist-to-height ratios, body composition parameters, cardiometabolic markers, and psychobehavioral measures, etc.) at weeks 12 and 24, longitudinal changes will be assessed using mixed-effects models. These models will account for within-participant correlations and missing data. A time-by-group interaction term will be included to evaluate whether there are significant differences in weight reduction between the study groups. The models will be adjusted for stratification factors (age, sex, and baseline BMI *z*-score) and corresponding baseline values to control for any potential systematic group differences at baseline.

Continuous variables will be compared using independent-sample *t*-tests or Mann–Whitney *U* tests, as appropriate. Categorical outcomes, including the proportions achieving predefined reductions in %BMI95 (≥ 5%, ≥ 10%, ≥ 15%) and AE incidence, will be analyzed using chi-square tests and logistic regression. Sensitivity analyses will be conducted to test the robustness of the results. A post hoc analysis will compare adherers and non-adherers, with adherence defined as attendance at ≥ 50% of scheduled visits during the 24-week study period. Exploratory dietary adherence will be defined at the participant level as not exceeding the group-specific upper limit at ≥ 50% of available post-baseline recalls. Participants with fewer than two post-baseline recalls will be considered not classifiable for dietary adherence analyses. Statistical significance will be set at a two-tailed *P*-value of < 0.05. All analyses will be performed using SPSS and R software.

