#### Inclusion criteria

Participants meeting all of the following criteria will be included in the study:Children aged 8 to 11 years, enrolled in grades 3 through 6 of primary school, at the time of providing informed consentDiagnosed with obesity according to the diagnostic criteria outlined in the Chinese Health Industry Standard (WS/T586-2018) “Screening for Overweight and Obesity in School-age Children and Adolescents” [38].Demonstrated clear willingness from both child and parent/guardian to participate in weight management interventions.Written informed consent from the legal guardians and assent from the child participants obtained prior to enrollment.

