### Randomization and allocation

Eligible participants will be randomized 1:1 to the ASER or control group using centralized, computer-assisted minimization with allocation concealment, balancing age (8–9 years vs. 10–11 years), sex (male vs. female), and baseline BMI *z*-score category (mild: + 1.645 ≤ z < + 2.5; moderate: + 2.5 ≤ z < + 3.0; severe: z ≥ + 3.0). To avoid treatment contamination, related participants from the same family will be allocated to the same intervention group. Randomization will be implemented by an independent statistician via a secure system; site investigators will enroll participants, submit baseline stratification variables, and receive the assignment, with the allocation sequence concealed from site staff until assignment. Due to the nature of the intervention, blinding of participants and intervention implementers is not feasible. However, health education physicians, data collectors, and outcome assessors/statisticians will remain blinded to group assignments throughout the study.

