#### Secondary outcomes

Body weight and body composition indicators:BMIz: Between-group differences at week 24; within-group changes from baseline at weeks 12 and 24.Degree of reduction in %BMI_95_ (≥ 5%, ≥ 10%, and ≥ 15%), waist-to-height ratio, and body composition parameters (fat mass index [FMI], fat-free mass index [FFMI], visceral fat area, body fat percentage): between-group and within-group changes at weeks 12 and 24.Growth and developmental indicators:Height, Tanner stage, annual growth velocity (GV), and height SDS changes from baseline, with between-group comparisons at weeks 12 and 24.GV (cm/year) = 12 * (current height – previous height)/(visit interval in months).Height SDS is calculated based on data from the 2005 Chinese National Growth Survey in nine cities [41]: Height SDS = (height at assessment time − mean height for same age/gender group)/standard deviation of height for same age/gender group).IGF-1 changes from baseline and between-group comparisons at week 24.Cardiometabolic risk factors and serum biochemical indicators:Blood pressure; serum biochemical indicators (high-sensitivity C-reactive protein, liver function, renal function, uric acid); lipid profile (total triglycerides, HDL-C, LDL-C); blood glucose at 0, 60, and 120 min during the oral glucose tolerance test (OGTT); insulin release test (IRT); area under the curve (AUC) for OGTT and IRT; homeostasis model assessment of insulin resistance (HOMA-IR) and β-cell function (HOMA-B): between-group and within-group changes at weeks 12 and 24Dietary and psychobehavioral parameters:Dietary quality (dietary balance index, dietary inflammatory index, etc.), dietary patterns, sleep, anxiety levels, and physical activity: between-group and within-group changes at weeks 12 and 24.Adverse events (AEs):AEs will be systematically monitored and recorded throughout the trial. Expected AEs in this low-risk intervention are mild.Between-group differences in the incidence of all AEs at weeks 12 and 24.

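### Baseline Tanner stage is implied as collected but left out of the covariate list; adding it would modestly sharpen the growth, IGF-1, insulin and body-composition comparisons, most clearly growth velocity

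*Protocol article*

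**What the plan says.** All references are to the protocol article.

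- Inclusion criteria: "Children aged 8 to 11 years, enrolled in grades 3 through 6 of primary school".
- Randomization and allocation: minimisation works by "balancing age (8–9 years vs. 10–11 years), sex (male vs. female), and baseline BMI *z*-score category".
- Statistical analysis: "The models will be adjusted for stratification factors", which the text lists as "age, sex, and baseline BMI *z*-score) and corresponding baseline values to control for any potential systematic group differences at baseline". Independent-sample t-tests or Mann–Whitney tests are also listed for continuous variables, without saying which outcomes they serve.
- Secondary outcomes: "Height, Tanner stage, annual growth velocity (GV), and height SDS changes from baseline, with between-group comparisons at weeks 12 and 24"; "IGF-1 changes from baseline and between-group comparisons at week 24"; and "GV (cm/year) = 12 * (current height – previous height)/(visit interval in months".

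Tanner stage therefore appears as an outcome and nowhere as a balancing factor or covariate. The growth outcomes and IGF-1 are not named in the mixed-model sentence; they fall under its closing et cetera.

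**The concern.** The age range spans years in which some children are prepubertal and others are not. Stage at entry can be expected to influence how fast height, IGF-1, insulin measures and fat-free mass change over 24 weeks, whatever the diet. An outcome's baseline value captures where a child starts, not how fast that child is about to change. Age and sex capture the rate only in part, because children of the same age band and sex differ in stage.

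Growth velocity shows the gap most plainly. It is computed from two trial visits, so no velocity exists at baseline and the rule of adjusting for the corresponding baseline value has nothing to act on. Any result taken from the t-tests or Mann–Whitney tests has no adjustment at all.

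At stake are the precision of these secondary comparisons and how readily they can be interpreted if the arms happen to differ in pubertal stage.

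**Working it through.** The plan gives no figure on this point, so there is none to reproduce. From Sample size estimation I take 82 children per group and 20% dropout: 82 × 0.8 = 65.6, about 65 per group (131 in all). Pubertal share and effect sizes are not in the document and are assumed.

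**1. How large could a chance imbalance be?** Under simple randomisation, the SE of the between-arm difference in pubertal share π is √(2π(1−π)/n).

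| n per arm | π | SE | 95% range | Chance of a gap ≥ 10 points |
|---|---|---|---|---|
| 82 | 0.20 | 0.062 | ±12 points | 11% |
| 82 | 0.35 | 0.074 | ±15 points | 18% |
| 82 | 0.50 | 0.078 | ±15 points | 20% |
| 65 | 0.20 | 0.070 | ±14 points | 15% |
| 65 | 0.35 | 0.084 | ±16 points | 23% |
| 65 | 0.50 | 0.088 | ±17 points | 25% |

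The trial balances on age band and sex, which shrinks this. In a simulation (4,000 runs per setting, pubertal share 34% and linked to age and sex, allocation balanced within age-by-sex cells), a gap of at least 10 points occurred in about 12 to 14% of trials with 164 children and 18 to 20% with 131.

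**2. Does omission cause error?** The same simulation analysed the outcome adjusted for age, sex and its baseline value, with and without stage. With no treatment effect, the rejection rate was 0.048 to 0.052 without stage and 0.047 to 0.053 with it. Average bias was about 0.

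**3. What does it cost in precision?** SE of the treatment effect with 164 children:

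| Residual pubertal effect (residual SD) | SE without stage | SE with stage | Excess |
|---|---|---|---|
| 0 | 0.1252 | 0.1256 | −0.3% |
| 0.3/0.8 ≈ 0.4 | 0.1265 | 0.1255 | 0.8% |
| 0.5/0.8 ≈ 0.6 | 0.1292 | 0.1255 | 2.9% |
| 0.8/0.8 = 1.0 | 0.1351 | 0.1256 | 7.6% |

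A hand check agrees. The four assumed age-by-sex cells have pubertal shares 0.100, 0.354, 0.269 and 0.646 (mean 0.342), so the average within-cell variance of stage is (0.090 + 0.229 + 0.197 + 0.229)/4 = 0.186. The outcome's baseline value, which differs by 0.8 between stages against a unit SD, reduces this to 0.186/(1 + 0.64 × 0.186) = 0.166. The SE ratio is then √(1 + 0.166 × effect²): 1.012, 1.032 and 1.080 for effects of 0.375, 0.625 and 1.0. Taking off the 0.3% cost of the extra parameter gives about 0.8%, 2.9% and 7.6%.

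With no baseline value to adjust for, as for growth velocity, 0.186 replaces 0.166 and the ratios are 1.013, 1.036 and 1.089 before that cost, slightly more.

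**4. What could one unlucky allocation do?** After balancing on age and sex, the imbalance had SD 0.068 with 164 children, so its 95% limit is 1.96 × 0.068 = 0.133. Times an effect of 0.6 SD, the shift is 0.08 SD. The SE of a difference is √(2/82) = 0.156 SD, so the shift is about half a standard error. This slightly overstates it where a baseline value absorbs part.

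The simulation uses one follow-up time and analysis of covariance, not the full mixed model, and ignores the BMI z-score category.

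**The case against.** The case for leaving the plan alone is substantial. Adjusting for the minimisation factors and the baseline value is conventional and coherent. Age and sex, which probably carry much of the pubertal variation, are both balanced and adjusted for. Baseline values absorb much of the stage difference in IGF-1, insulin and body composition, and height SDS is standardised for age and sex. The article is a condensed account: it promises unspecified sensitivity analyses, and an analysis plan not shown could add this covariate. All of that stands, and it keeps the point small. It does not remove it, because the article names its covariates and stage is not among them.

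Three stronger readings are tempting and are not supported.

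- A reader might infer that pubertal imbalance could mimic or hide a diet effect and so invalidate the comparison. Randomisation already accounts for that variability in the standard error; step 2 shows no average bias and no type I inflation. Only the conditional statement in step 4 survives.
- A reader might infer that a claim of safety for growing children rests on these outcomes. The Discussion makes no such claim: it presents growth monitoring as part of ethical rigour and does not mention IGF-1.
- A reader might infer that the primary endpoint is at risk. BMI z-score is standardised for age and sex and adjusted for baseline, and nothing in the document shows a material effect of stage on it at week 12.

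**Conclusion.** The point holds as a minor improvement to a stated method. A likely predictor of change, whose baseline value is implied by the outcome list, is missing from the covariates for the growth, IGF-1, insulin and body-composition outcomes. The loss is precision on secondary outcomes: about 1 to 8% in the standard error, marginally more for growth velocity. A residual allocation imbalance could move one trial's estimate by about half a standard error at the outer end.

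These sizes rest on an assumed 34% pubertal share and residual effects of 0.4 to 1.0 SD. If stage adds nothing beyond age, sex and baseline value, the gain is nil and the cost is about 0.3% of the standard error. That stage matters for these outcomes is a general expectation, not something the document quantifies.

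**What to change.** - Pre-specify baseline Tanner stage (1 versus 2 or more) as a covariate in the models for growth velocity, height, height SDS, IGF-1, body composition, HOMA-IR and HOMA-B, and the OGTT and insulin areas under the curve. Use the baseline reading only; later stage is itself an outcome and may respond to treatment.
- State that between-group inference for these outcomes comes from the adjusted models, not from the t-tests or Mann–Whitney tests.
- For week-12 BMI z-score, leave the primary model unchanged and add baseline stage only in a sensitivity analysis.
- Show baseline stage by arm in the baseline table.

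The change is to analysis wording and should be fixed before outcome data are analysed, so that it cannot look like a response to an observed imbalance. It needs no new data, provided stage is recorded at baseline as the change-from-baseline outcome implies, and no change to the minimisation. It costs one degree of freedom per model and a stated rule for children whose baseline stage is missing.

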### Intervention measures

Children in the ASER group are required to consume no more than 30–35% of their target total daily energy intake during the period from after-school (17:30) until bedtime. The target total energy intake during the weight loss phase is based on the age-appropriate estimated energy requirement for healthy children, reduced by 300–500 kcal. Dinner must begin no later than 19:00 local time. Energy intake is not restricted during other time periods, but healthy eating guidance is provided, including recommended portions of fruits, vegetables, and dairy products to ensure adequate nutrition.

Dietitians will calculate dinner and post-dinner snack portions based on each child’s eating habits and the Acceptable Macronutrient Distribution Ranges (AMDR) recommended for children [40], and will develop individualized dietary plans. Nutrition education will be provided to the caregivers using food models or photographs. Caregivers are advised to weigh foods during meal preparation and to keep detailed records. To enhance compliance, one evening per week may be designated as a “free day,” during which energy intake is not strictly restricted.

The first 12 weeks constitute the intensive intervention phase, followed by a maintenance phase from weeks 13 to 24. In the first week, caregivers are required to record and submit daily dietary logs and food photographs via a designated WeChat group, with particular emphasis on the period from after-school to bedtime, to facilitate monitoring and guidance by the research team.

During the intensive intervention phase, dietary intake will be assessed at weeks 4 and 8 using 24-h dietary recalls. At these interim visits, participants will also receive face-to-face guidance, health education, and anthropometric measurements. In the maintenance phase, participants are expected to continue following the prescribed dietary plan.

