Participants in the control group will receive standard clinical dietary advice for weight management based on the Nutritional Guidelines for Weight Management of School-Aged Children [35], which include recommendations on energy intake and healthy dietary patterns. The mode and frequency of feedback and supervision will be consistent with those of the intervention group. Both groups will receive regular health education on lifestyle topics, including balanced nutrition, physical activity, and sleep hygiene. Comprehensive assessments, including food frequency questionnaires (FFQ), 24-h dietary recalls, anthropometric measurements, body composition analysis, laboratory tests, and relevant questionnaires, will be conducted at baseline (week 0), week 12, and week 24. During the study period, participants will be asked not to engage in any additional weight-loss interventions, including other dietary programs, medications, or structured exercise regimens outside of their usual activities. Routine pediatric care and non-weight-related treatments will be allowed.

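### Adherence is defined by attendance at the visits that also supply the outcomes, so it is confounded with missing data and does not measure following the evening limit

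*Protocol article*

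**What the plan says.** The Statistical analysis section gives two definitions of adherence.

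- **Attendance.** "A post hoc analysis will compare adherers and non-adherers, with adherence defined as attendance at" at least "50% of scheduled visits during the 24-week study period".
- **Dietary, labelled exploratory.** A child is adherent by "not exceeding the group-specific upper limit at" half or more of the available post-baseline recalls. A child with fewer than two such recalls is not classifiable.

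The visits are described under Intervention measures. In the intensive phase, "dietary intake will be assessed at weeks 4 and 8 using 24-h dietary recalls", and at these visits "participants will also receive face-to-face guidance, health education, and anthropometric measurements". Full assessments, including recalls, take place at weeks 0, 12 and 24. The control arm follows the same pattern: "The mode and frequency of feedback and supervision will be consistent with those of the intervention group". The same section allows ASER families one evening a week "during which energy intake is not strictly restricted".

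The primary outcome is the between-group difference in BMI z-score change at week 12. Under Quality control and data management, the protocol undertakes to try to collect outcomes from children who withdraw or deviate, above all at weeks 12 and 24.

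**The concern.** An adherence variable should record whether the child followed the assigned intervention, and it should be separable from whether the outcome was observed. The attendance rule does neither. ASER is an evening energy limit, and coming to the clinic is not evidence of keeping to it. A child who misses visits also misses measurements, so the non-adherent group consists mainly of children with little outcome data.

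The rule can also label children the wrong way round. A child who gave up the diet but is successfully retrieved at weeks 12 and 24 has attended two of four visits and counts as an adherer.

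The dietary definition is closer to the right idea, but it states no exception for the free evening. A recall covering that evening can count against a child who did what the plan permitted.

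At stake is the interpretation of the result. The Discussion puts forward better adherence as part of the case for ASER, and this comparison can say very little about it.

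**Working it through.** The protocol gives no figure for this comparison, so there is none to reproduce.

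**Inputs from the protocol.** Post-baseline visits at weeks 4, 8, 12 and 24; 50% threshold; 164 children; expected dropout 20%; difference 0.14 with SD 0.28 (Sample size estimation).

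**Step 1: who is a non-adherer.** Without baseline, fewer than 50% means fewer than 2 of 4 visits. With baseline counted, 2 of 5 (40%) fails and 3 of 5 (60%) passes. Either way a non-adherer has at most one post-baseline visit. Of the 2^4 = 16 attendance patterns:

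| Class | Patterns | With week 12 | With weeks 12 and 24 |
|---|---|---|---|
| Non-adherer | 5 (none; week 4, 8, 12 or 24 only) | 1 | 0 |
| Adherer | 11 | 7 | 4 |

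If children drop out and do not return, the only non-adherer patterns are none and week 4 only, and neither contains an endpoint. Conversely, a child seen only at weeks 4 and 8 is an adherer with no week-12 or week-24 value.

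**Step 2: dependence on visits after the endpoint.** Take a child who misses weeks 4 and 8 and attends week 12. The child is a non-adherer if week 24 is missed and an adherer if it is attended, with the same week-12 value in both cases.

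**Step 3: how many non-adherers have a week-12 value.** Assume independent attendance with probability q at each visit.

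- P(non-adherer) = (1−q)^4 + 4q(1−q)^3
- P(non-adherer with week 12) = q(1−q)^3

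| q (assumed) | Non-adherers of 164 | Of these, with week 12 |
|---|---|---|
| 0.6 | 29.4 | 164 × 0.6 × 0.064 = 6.3 |
| 0.7 | 13.7 | 164 × 0.7 × 0.027 = 3.1 |
| 0.8 | 4.5 | 164 × 0.8 × 0.008 = 1.05 |
| 0.9 | 0.6 | 164 × 0.9 × 0.001 = 0.15 |

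Over this range a week-12 value is present in 21–24% of non-adherers and 68–90% of adherers.

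**Step 4: a more generous case.** Suppose all 0.20 × 164 ≈ 33 expected dropouts are non-adherers, and that m of them have a week-12 value, compared with 131 adherers. Power for 0.14 is Φ(0.14 / [0.28 √(1/m + 1/131)] − 1.96):

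- m = 3.3 (10% of 33): 14%
- m = 8.25 (25%): 29%
- m = 16.5 (50%): 48%

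**Step 5: the free evening.** Assume four recalls on random days, a free evening taken every week by every child, and the limit always exceeded on it. A child within the limit on a fraction p of other evenings is then within it on p × 6/7 of recalls. Adherent means X ≥ 2, with X binomial on 4 recalls.

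- p = 0.60, no free-evening effect: 1 − 0.4^4 − 4(0.6)(0.4^3) = 82%
- p = 0.60, with it (0.514 per recall): 71%
- p = 1, with it (6/7 per recall): 1 − (1/7)^4 − 4(6/7)(1/7)^3 = 99%

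**The case against.** The strongest reply is that the comparison is labelled post hoc, dietary adherence is labelled exploratory, and the primary analysis is intention-to-treat with mixed models. No conclusion of the trial is tied to the adherer comparison, and the protocol nowhere calls it a randomised one. All of that stands, and it limits how much the point matters.

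A reader might go further and infer that the comparison cannot be made at all, or that it sets children with data against children without. The documents do not support that. A child seen only at week 12 or only at week 24 is a non-adherer with an endpoint. Weeks 4 and 8 include anthropometry, so four of the five non-adherer patterns yield a post-baseline BMI z-score that a mixed model can use. Outcome retrieval is planned.

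The counts also rest on the visits named in the text, because the schedule figure (Fig. 1) was not available to this review. With two further post-baseline visits, for example, a child attending 2 of 6 would be a non-adherer and could have both endpoints.

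It is also fair to say that the protocol already has an intake-based definition. It does not rescue the attendance comparison, however. With one recall per visit, a child who attends at most one post-baseline visit has at most one recall and is not classifiable. Lastly, the free-evening effect depends on assumed behaviour (the protocol only permits such an evening) and is small for children who otherwise comply.

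**Conclusion.** The point holds in a limited form. The attendance rule is stated in the protocol, is confounded with missing outcomes, uses attendance after the primary endpoint, and does not measure the intervention. On the named visits, and with assumed independent attendance of 0.6 to 0.9, between about 6 and 0.15 of 164 children would be non-adherers with a week-12 value. Even if half of all expected dropouts were such children, power for the planning difference would be about 48%. The comparison is close to uninformative, not impossible.

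The free-evening fault is secondary: 71% instead of 82% classified adherent for a child compliant on 60% of other evenings, under the assumptions of step 5, and little change for a fully compliant child. Neither fault touches the primary intention-to-treat result. The definitions should still be changed, because they misclassify and the data for a better definition are already planned.

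**What to change.** 1. Report visit attendance as retention or engagement, not as adherence to the intervention.
2. For week 12, define ASER adherence from the recalls up to week 12, against the child's own prescribed evening limit.
3. Record at each recall whether it covers the designated free evening, and leave such recalls out of both numerator and denominator.
4. Compare energy intake from 17:30 to bedtime, and over 24 h, between the randomised arms on one scale, using the recalls already planned.
5. Describe any adherer versus non-adherer comparison as non-randomised.

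A complier-average analysis is optional. It would need a notion of compliance that works in both arms, although no evening limit is stated for controls, and an exclusion restriction that is open to doubt because ASER also brings individualised plans.

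**Cost.** One item on the case report form, a small extra analysis and a few lost recalls. With three recalls up to week 12, a 1 in 7 chance that each falls on a free evening, and the existing two-recall minimum, (1/7)^3 + 3(6/7)(1/7)^2 = 19/343, or about 5.5% of fully attending children, would become not classifiable. Low attenders remain unclassifiable under any definition based on recalls taken at visits.
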